## The Present Study

To fill this gap, the purpose of this paper, therefore, was to consider how a more rigorous controlled study of the effectiveness of education support services for students with chronic health conditions could be undertaken. Specifically, it outlines the protocol for a feasibility study as a first stage to evaluating the effectiveness of these programs. Feasibility studies are considered useful as preparation for the conduct of a larger controlled evaluation of complex interventions (Thabane et al., 2016), with the goal of reducing uncertainty and thereby increasing the chance of a successful larger study (Thabane et al., 2016). The proposed protocol is based upon and includes recommended and relevant sections of the Standard Protocol Items: Recommendations for Interventional Trials (SPIRIT) checklist (Chan, Altman, Dickersin, & Moher, 2013).

Specifically, the aims of the feasibility study are to:

Examine the effectiveness of an education support program for school-aged students with chronic health conditions on their engagement in education and learning, and quality of life;Trial the recruitment and retention of study participants;Identify and trial the use of validated outcome measures;Obtain feedback from stakeholders about the feasibility of the above with the view of conducting a larger scale trial.

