### Sample Size and Power Analysis

Sample size calculations were run to determine the number of participants required in the study to have an 80% chance of detecting a 0.3 standard deviation effect of the intervention based on the results of the outcome measures. Based on these criteria, we would need complete data from 180 participants in each arm of the study. Attrition and loss to follow-up is considered to be low, in the order of 25%.

As such, we would need to recruit 240 participants to each arm of the study. However, as this is a feasibility study, we will recruit 40 participants to each arm of the trial and evaluate the procedure used, time, and feasibility of achieving a larger sample for any future larger-scale study.

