### Data Analysis

The primary and secondary outcomes form the dependent variables in this research. The independent variables include being in receipt of the intervention or not being in receipt of the intervention (i.e., membership of either the intervention or the control group).

Quantitative data will be analyzed descriptively. Continuous or scale data will be analyzed using analysis of variance (ANOVA), and we will report group means and standard deviations. We will control for confounders as previously described. We will use the data and variables of the number and type of education support activities as a measure of dose and perform sensitivity analysis. Qualitative data obtained from stakeholder interviews will be analyzed thematically.

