## Discussion and Conclusion

This protocol paper provides information about how a feasibility study could be undertaken to obtain robust information about the effectiveness of an education support program for hospitalized students with chronic health conditions. While the protocol was developed to evaluate the effectiveness of the education support program at the Royal Children’s Hospital in Australia, the study design is potentially replicable for evaluating other hospital-based education support programs for children and young people with chronic health conditions.

To date, evidence of effectiveness of education support programs for this group of children and young people is dominated by qualitative research, case studies, and expert opinion. More robust evidence is needed. Importantly, this feasibility study protocol tackled some important questions or considerations, including developing an answerable research question, choosing a controlled study design that compares the outcomes of both an intervention group and a well-matched non-intervention or control group, eligibility criteria, important and validated outcome measures, and how data should be analyzed and reported. The use of relevant and validated outcome measures, in particular quality of life, and consistent reporting of results using group means and standard deviations, is particularly important for future research in this field. Doing so would allow for comparing and even pooling results from different studies, thus providing even more robust evidence of the effectiveness of education support programs. To date, this has not been possible due to significant inconsistencies in these areas across the small number of controlled studies in this field.

Feasibility studies are considered useful as preparation for the conduct of a larger controlled evaluation of complex interventions (Thabane et al., 2016) by providing information about the feasibility of a main or larger study, with the goal of reducing uncertainty, and thereby increasing the chance of a successful larger study. As such, the current feasibility study includes a qualitative component to review and assess important aspects of the implementation of the trial, including recruitment, administering the measurement tools, and follow-up with trial participants. Such experience and learnings would be useful for preparing for any future larger study.

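### Aim 1, the primary outcome and the ANOVA address effectiveness, but the 40 per arm is a feasibility number: recast effectiveness as estimation and make recruitment and retention rates the main outcomes (should fix)

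*Protocol article*

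**What the plan says.** In the protocol article, The Present Study lists four aims. The first is to "Examine the effectiveness of an education support program for school-aged students with chronic health conditions on their engagement in education and learning", together with quality of life. The second is "Trial the recruitment and retention of study participants".

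The PICO question (Developing an Answerable Research Question) asks whether supported children do better than unsupported ones on engagement and quality of life. Engagement is the primary outcome and quality of life the secondary.

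Sample Size and Power Analysis seeks enough participants "to have an 80% chance of detecting a 0.3 standard deviation effect of the intervention" and concludes that "we would need complete data from 180 participants in each arm of the study". It allows for 25% attrition, arrives at 240 recruited per arm, and continues: "However, as this is a feasibility study, we will recruit 40 participants to each arm of the trial". The stated purpose of the 40 is to assess procedure, time and whether a larger sample could be reached.

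Data Analysis says: "The primary and secondary outcomes form the dependent variables in this research". It announces a descriptive analysis of the quantitative data. It then prescribes ANOVA for scale data with control for confounders, and a sensitivity analysis using the amount of support received as dose. Discussion and Conclusion adds that "the current feasibility study includes a qualitative component to review and assess important aspects of the implementation of the trial", and names recruitment, use of the measures and follow-up among those aspects.

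**The concern.** Calling the study a feasibility study justifies 40 per arm only if the aims, the main outcome and the analysis are also those of a feasibility study. Here the question that 40 per arm cannot answer has first place: it is Aim 1, it supplies the primary outcome, and it is what the ANOVA compares. The questions that 40 per arm can inform, such as how many eligible families consent and how many remain at six months, are not named as outcomes.

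An ANOVA at this size will most likely be non-significant even if the 0.3 SD effect is real. In an unadjusted comparison it can be significant only if the observed difference is well above 0.3 SD. Either result could mislead if reported under an aim worded as effectiveness. The article itself says that only four controlled studies were found in this field, so one more imprecise result could carry undue weight.

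**Working it through.** **Inputs.** From Sample Size and Power Analysis: target effect d = 0.3 SD, power 80%, 180 complete per arm, attrition 25%, 240 recruited per arm needed, 40 per arm planned. Alpha and sidedness are not stated; I assume 5% two-sided. Equal arms; SD set to 1 because the effect is standardised.

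**1. The plan's own figures.**
- n per arm = 2(z₀.₉₇₅ + z₀.₈₀)²/d² = 2(1.960 + 0.842)²/0.3² = 174.4, so 175 (176 by the noncentral t). The stated 180 is within 3% and gives 81% power.
- A one-sided 5% test would need 138, which does not match, so two-sided 5% is the natural reading.
- Recruitment: 180/(1 − 0.25) = 240, exact.

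The plan's arithmetic is therefore sound. Planned recruitment is 40/240 = one sixth of the stated need, and leaves 40 × 0.75 = 30 completers per arm.

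**2. What 40 per arm delivers for the effectiveness comparison (no covariates).**
Power ≈ Φ(d√(n/2) − 1.96), checked with the noncentral t. The 95% CI half-width is t × √(2/n), with 2n − 2 degrees of freedom.

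| | 30 completers per arm | 40 per arm, no attrition |
|---|---|---|
| d√(n/2) | 1.162 | 1.342 |
| Power, normal approximation | 21.2% | 26.8% |
| Power, noncentral t | 20.8% | 26.3% |
| Effect detectable with 80% power | 0.74 SD | 0.63 SD |
| 95% CI half-width | 2.002 × √(2/30) = 0.52 SD | 1.991 × √(2/40) = 0.45 SD |

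Both half-widths exceed 0.3 SD, so an observed difference of exactly the target size would have an interval that includes zero. With 30 per arm, an unadjusted difference must exceed about 0.52 SD to be significant, which is 0.52/0.3 ≈ 1.7 times the target.

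**3. Does baseline adjustment rescue it?** Baseline outcomes are collected. The documents give no baseline-to-follow-up correlation r, so a range is assumed. Residual SD = √(1 − r²).

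| Assumed r | Residual SD | Power, 30 per arm | Power, 40 per arm |
|---|---|---|---|
| 0.5 | 0.87 | 27% | 34% |
| 0.6 | 0.80 | 31% | 39% |
| 0.7 | 0.71 | 37% | 47% |

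It does not. Even at r = 0.7 with no attrition, the half-width is about 0.445 × 0.714 = 0.32 SD.

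**4. What 40 per arm delivers for feasibility.** If attrition is at the plan's 25%, the Wilson 95% CIs are:
- 10 of 40 lost in one arm: 14% to 40%.
- 20 of 80 lost overall: 17% to 35%.

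This bears directly on the 240. If attrition were 40%, for illustration, 180 completers would need 180/0.60 = 300 recruits per arm.

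**The case against.** The strongest defence is that nothing is hidden. The section gives the powered size, says the study will not reach it and says why. No passage claims 80% power with 40 per arm. Data Analysis announces a descriptive analysis and reports means and SDs, which the discussion values for comparison and pooling across studies. No significance level or decision rule on effectiveness is given. All of this stands, so the small sample is not the error. But the sentence after the descriptive one prescribes ANOVA with confounder control. That is a between-group comparison, and it sits under an aim worded as effectiveness.

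A reader might go further and infer three things that the document does not support:

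- **That the 25% attrition cannot be checked, or that the study cannot inform a larger trial.** Retention is part of Aim 2, the denominator is fixed at 40 per arm, and follow-up is at 3 and 6 months, so retention can be counted. Time and procedure are also to be assessed, and ten stakeholder interviews (two at each of five sites) are planned.
- **That recruitment and follow-up are assessed only by interview.** The discussion says the study includes a qualitative component; it does not say there is no other. The sentence on dependent variables can be read as describing the group comparison only.
- **That the absence of progression thresholds is a defect.** A condensed article commonly leaves these to the full protocol.

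It is also fair that 21% is the low end of the power range, because it ignores adjustment. The upper end under the assumed correlations, 47%, is still far below 80%.

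**Conclusion.** The point holds as a mismatch within the stated plan. The sample was cut to a feasibility size, but the first aim, the primary outcome and the main analysis were left as those of an effectiveness study, and only engagement and quality of life are named as dependent variables.

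For the plan's own 0.3 SD target, power is about 21–26% unadjusted and about 27–47% with adjustment at assumed baseline correlations of 0.5 to 0.7. The unadjusted 95% CI half-width is 0.45–0.52 SD. These figures assume a two-sided 5% test, equal arms and attrition between zero and the plan's 25%.

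Severity: should fix. The plan is open about the reduced sample and will yield usable retention data. The change governs what may be concluded, not whether the study is worth running.

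**What to change.** 1. Reword Aim 1 and Data Analysis so that the group difference and the SDs are estimated with 95% CIs. State that no hypothesis test will be done and no conclusion on effectiveness drawn.
2. Make these the primary feasibility outcomes, by arm with 95% CIs: the proportion of eligible patients who consent, the recruitment rate, 6-month retention and questionnaire completeness. Compare retention explicitly with the 25% attrition behind the 240.
3. Keep engagement and quality of life as the measures being tried out, with their means and SDs reported as now planned.
4. Any progression criteria are for the investigators to set, and should allow for sampling error. For example, if true retention is exactly 75%, the chance of seeing at least 30 of 40 retained is about 0.58 in one arm. For both arms, taken as independent, it is about 0.58² = 0.34. A rule set at the assumed rate itself would therefore fail about two times in three even though the assumption was right.

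Cost: changes of wording, a screening log to supply the denominator for consent, and a more modest claim. No additional participants are needed.

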### Outcomes, Confounders, and Measurement Instruments

#### Primary outcome: Engagement in education and learning

We will use a short form of the validated Attitudes to School Survey developed by Khoo and Ainley (2005) and used in the *Longitudinal Study of Australian Children*. The survey has been used and referred to by the authors as a measure of school engagement as it aims to measure aspects of the complex relationship between engagement, attitudes, and motivation in terms of their influence on intentions to participate in school and schoolwork. The survey includes a primary and a secondary school version each consisting of 30 statements that cover 5 domains: students’ general satisfaction with school, their motivation, their attitudes toward their teachers, their views on the opportunities their school provides, and their sense of achievement. Students are asked to indicate their level of agreement on a 4-point Likert scale ranging from *strongly agree* to *strongly disagree*.

*General Satisfaction*, sometimes called positive affect, reflects favorable feelings about school as whole. A typical item is *my school is a place where I really like to go each day*.*Motivation* represents a sense of self-motivation in learning and that learning is enjoyable for its own sake. A typical item is *my school is a place where I get excited about the work we do*.*Achievement* reflects a sense of confidence in one’s ability to be successful in school. A typical item is *my school is a place where I am good at schoolwork*.*Opportunity* represents a belief in the relevance of schooling for the future. A typical item is *my school is a place where what I learn will be useful*.*Teachers* refers to a feeling about the adequacy of the interaction between teachers and students. A typical item is *my school is a place where my teacher listens to what I say*.

We have developed a short form (15 statement) version, anticipating that the full version would be potentially too burdensome for the hospitalized and chronically ill child or young person. Items were chosen on the basis of their face validity/perceived appropriateness by the author, who had more than three years’ experience working with hospital-based teachers/educators and young people at the Royal Children’s Hospital in Melbourne, Australia, 2012–2016.

There are two ways to score the items: (a) calculate the total level of agreement and (b) calculate a scale score for the domains and survey as a whole. We will use the latter method as we are interested in the overall mean values of both the intervention and the control groups and related standard deviations.

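### The primary outcome is an in-house 15-item cut of a 30-item survey, so the validation claimed for the outcome measures cannot be assumed for it, and no check of it is described.

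*Protocol article*

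**What the plan says.** Under Primary outcome, the article states: "We will use a short form of the validated Attitudes to School Survey". It describes the parent instrument: "The survey includes a primary and a secondary school version each consisting of 30 statements that cover 5 domains". It then says "We have developed a short form (15 statement) version", because the full version was expected to burden ill children too much. On selection it says: "Items were chosen on the basis of their face validity/perceived appropriateness by the author", and supports that judgement by more than three years of work with hospital educators and young people at the Royal Children's Hospital.

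Of two scoring methods, the plan takes the one that will "calculate a scale score for the domains and survey as a whole". The reason given is interest in the overall group means and standard deviations.

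Aim 3 in The Present Study is to "Identify and trial the use of validated outcome measures". The abstract also calls the outcome measures validated. The Discussion and Conclusion recommends validated measures, quality of life in particular, together with consistent reporting of means and standard deviations, and adds: "Doing so would allow for comparing and even pooling results from different studies".

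**The concern.** Evidence of validity belongs to a set of items scored in a given way. Removing half the items can change what the total measures, how the domains are weighted and how reliable the score is. Here the selection used no item statistics, and the article reports no pilot, no reliability and no agreement with the full form. Neither Data Collection nor Data Analysis describes a step that would supply any of these.

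The study could therefore end with aim 3 apparently met although, for its primary outcome, the question was never examined. A later trial that keeps the same form would start with the same gap, and a reader might set its scores beside full-form scores from other studies without grounds for doing so. This is not a detail that an analysis plan could settle afterwards: the article itself fixes the instrument and makes the claim about it.

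**Working it through.** **1. The statements side by side.**

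| Place in the article | What it attaches 'validated' to | Instrument used |
|---|---|---|
| Primary outcome | The 30-statement parent survey | 15 statements chosen by the author |
| Secondary outcome | The 23-item PedsQL | PedsQL, no shortening described |
| Abstract; aim 3; Discussion | The outcome measures in general | Both of the above |

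The Primary outcome section is accurate and open about the shortening. The mismatch arises where the general statements cover the engagement measure as well. For the PedsQL they stand.

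**2. The plan's own sample size.** Sample Size and Power Analysis asks for an "80% chance of detecting a 0.3 standard deviation effect of the intervention based on the results of the outcome measures" and gives 180 complete per arm and 240 recruited. With two-sided alpha 0.05 (assumed, since alpha is not stated):

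- n = 2 × (1.960 + 0.842)² / 0.3² = 174.4, so 175 per arm (176 by the t-test), within 3% of 180.
- 180 / (1 − 0.25) = 240, an exact match.

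There is no arithmetic error here. The point about measurement does not depend on these figures.

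**3. What halving a scale can cost (illustration).** The documents give no reliability, so full-form values of 0.90 and 0.95 are assumed. Spearman–Brown also assumes that kept and dropped items are interchangeable.

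- Reliability of the half-length form: h = 0.5r / (1 − 0.5r).
- Sample-size ratio for the same true effect: r / h = 2 − r.
- Standardised effect, if 0.3 SD holds on the full form: 0.3 × √(h / r).

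| Full-form r | Short-form h | Ratio | Effect (SD) | n per arm | Recruited, 25% loss | Power at 180 |
|---|---|---|---|---|---|---|
| 0.95 | 0.905 | 1.05 | 0.293 | 184 | 246 | 79% |
| 0.90 | 0.818 | 1.10 | 0.286 | 192 | 256 | 77% |

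The comparison value for n is 175, and power at 180 without any loss of reliability is 81%. For the total score the loss is modest.

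**4. Domain scores.** The split of items over domains is not given. If it is even, 30 / 5 = 6 items per domain become 15 / 5 = 3. With an assumed six-item reliability of 0.70 to 0.80, the same formula gives 0.54 to 0.67. Domain scores are the weaker part of the planned scoring.

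**5. How precisely this study could check the form.** The approximate standard error of ln(1 − alpha) is √[2k / ((k − 1)(n − 2))], with k = 15. For an observed alpha of 0.818:

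- n = 80: standard error 0.166, 95% CI 0.75 to 0.87.
- n = 40 (one school version, if the 80 split evenly): standard error 0.237, 95% CI 0.71 to 0.89.

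This is informative but wide, so intervals are needed.

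**6. Why a short-with-full correlation would mislead.** The 15 items are part of the 30. If the two halves have equal variance and correlate at ρ, the short form correlates with the full form at √[(1 + ρ) / 2]. Even at ρ = 0 this is 0.71, and at ρ = 0.818 it is 0.95. The correlation with the omitted items is the informative one. At 0.818 in 40 children its 95% CI (Fisher z) is about 0.68 to 0.90.

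**The case against.** The other side has a good deal in its favour.

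- **Disclosure.** The Primary outcome section applies the word validated to the parent survey and states the shortening, its reason and the method of selection. This stands. It confines the fault to the general statements elsewhere and to the absence of a described check.
- **Pooling.** A reader might infer that the pooling argument fails altogether. It does not: the discussion singles out quality of life, and no shortening of the PedsQL is described. Only its extension to engagement scores lacks support.
- **Bias.** Because the author's experience was at the intervention hospital, a reader might infer that the items favour the programme. The documents do not support this. The items come from an existing survey, the examples shown concern the child's own school in general terms, and no mechanism is apparent.
- **Size.** From the domain scores one could claim a need for 20 to 30% more children (ratios 1.20 and 1.30 at assumed reliabilities of 0.80 and 0.70). That should not be the headline. The stated interest is in overall means, for which the illustration gives 5 to 10%, and recruitment here is fixed at 40 per arm for feasibility.
- **Feasibility purpose and article format.** Trialling measures is an aim, stakeholder feedback is planned, and a condensed article may omit routine reliability reporting. This softens the consequence. It does not remove the conflict between the general claim of validation and the primary instrument.
- **Burden.** Giving all 30 items to every ill child would undo a deliberate choice. This objection stands, and the fix below does not require it.

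**Conclusion.** The concern holds in a limited form. The primary outcome has not been shown to have the property that the abstract, aim 3 and the discussion give to the outcome measures, and the article describes no step that would show it. Validity and comparability with full-form scores are untested. It would go too far to conclude that they are absent, or that a result on the short form could not be interpreted at all.

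The main consequence is for interpretation and comparison across studies. Any loss of power is secondary and illustrative: about 5 to 10% more children in a later trial for the total score. That rests on an assumed full-form reliability of 0.90 to 0.95, on interchangeable items and on the 0.3 SD effect holding on the full form. The facts about the instrument are certain from the text; the magnitude is not.

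**What to change.** 1. **Wording.** In aim 3 and the discussion (and the abstract, for consistency), call the engagement measure 'adapted, not yet validated'. Limit the comparability and pooling statement to measures used intact. This costs nothing.
2. **Endpoint.** Name the total short-form score as the primary outcome and treat domain scores as exploratory. This agrees with the stated interest in overall means and costs nothing.
3. **Check on data already collected.** Report internal consistency, item-total correlations and completion rates by school version, with confidence intervals, as a feasibility result under aim 3. This needs item-level responses to be kept and a short analysis. With 80 children the intervals will be wide, and the report should say so.
4. **Optional.** Give the 15 omitted items once, at baseline and after the short form, to a random subsample. Correlate the short form with the omitted items, or correct for overlap, rather than using the full 30. The downside is added burden for those children. The gain is direct evidence on whether the short form tracks the rest of the survey, and on whether 30 items are in fact too many.
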